**FIGURE 1 bco270014-fig-0001:**
[figure not shown]
Patient pathway through study.

Immediately following the consultation, participants in both arms of the study who consented to have their consultation audio and/or video recorded will have their consent for the use of that recording confirmed and will be asked to provide further written consent for the use of that data. If at that stage any participants do not wish us to keep the recordings, they will be deleted.

All clinicians based in the participating hospitals who currently conduct follow‐up consultations with patients following surgery for kidney cancer will be eligible to take part in the study. They will be invited to participate by the local Principal Investigators at each site and will be asked to consent to take part in the study. Additionally, they will be asked if they agree to have their consultations audio‐ or video‐recorded and if they consent to being contacted to arrange an interview.

### Intervention

5.2

Patients in the SOC arm will have a consultation in which their pathology results, the risk of recurrence based on the Leibovich score and their follow‐up care plan are discussed. Within this usual care arm, patients are typically informed of the individual Leibovich score (0–11) and if this places them in the low, intermediate or high risk for recurrence group. They may also be told what the estimated average 5‐year absolute risk of recurrence for that risk group is as a percentage.

For patients in the intervention arm, the consultation will include the use of the new PREDICT Kidney tool to support the conversation about the risk of recurrence and risk‐stratified follow‐up. After the clinician has explained the pathology results and confirmed that the patient has kidney cancer, the clinician will enter the patient's risk factor information into the online PREDICT Kidney tool. The PREDICT Kidney tool is a risk‐communication tool that implements the augmented Leibovich model. It presents the risk of recurrence category based on the Leibovich score, alongside the 1‐year, 5‐year and 10‐year absolute risk of recurrence based on the Leibovich model and the 1‐year, 5‐year and 10‐year age‐ and sex‐matched absolute risk of death from other causes calculated using joint modelling with Cox proportional hazard models approach to include competing risks as applied in the development of the PREDICT Breast and PREDICT Prostate tools^18^, ^19^ (Figure 2).

**FIGURE 2 bco270014-fig-0002:**
[figure not shown]
Screenshots of the PREDICT kidney tool: A) the landing page, B) the input section, C) icon array visualisation of kidney cancer recurrence, other cause of death and recurrence‐free survival, one of five visualisations available in the tool, and D) the information provided in the printout.

Training on the PREDICT Kidney tool will be provided for the clinicians after the recruitment of control participants is complete to limit any contamination of the SOC consultations. The clinicians will be given a guidance document outlining how to best use the tool to communicate personalised risk estimates using the text and graphics generated. Each patient will be given a printed report from the tool at the end of their consultation including graphic results, what they mean, and links to more information and support. The design of the tool, the format of the risk visualisations and the report have been informed by the existing PREDICT Breast and PREDICT Prostate tools, the wider literature^20^ and a series of online workshops carried out by the research team. Workshops were conducted with: patients with experience of kidney cancer, members of the public without a history of kidney cancer and healthcare professionals involved in the care of patients with kidney cancer.

### Sample size

5.3

We aim to recruit 30 patients to each arm (a total of 60). This will enable us to assess the recruitment rate to within +/− 10% with 95% confidence intervals (point estimate 50%). This number of participants is also sufficient to enable data collection for the qualitative components of the analysis.

### Data collection

5.4

Before their consultation, study participants in both arms will be asked to complete a baseline paper questionnaire (File S1) asking about sociodemographic factors, health literacy,^21^ subjective and objective numeracy^22^, ^23^ and general health (measured using the EQ‐5D‐5L)^24^ (Table 2). Immediately following their consultation, study participants in both arms will be asked to complete a second paper questionnaire (File S2) including outcome measures relating to comprehension of risk of recurrence and follow‐up, perceived risk of cancer recurrence, risk conviction, satisfaction with the information provided and fear of cancer recurrence (Table 2). Subjective comprehension will be measured by averaging two Likert items asking: “How clear was the information you were given about ….? ” and “How much effort did you have to put in to understand the information you were given about ….? ”. Objective comprehension will be measured with a single question asking: “Which of these risk categories best describes your risk of cancer recurrence?”. Perceived risk of cancer recurrence will be measured using one question on a scale of 0–100 and a measure of risk conviction based on two questions used in previous studies.^25^ Fear of cancer recurrence will be measured using the first six questions from the Fear of Cancer Recurrence Inventory short form (FCRI‐SF)^26^).

**TABLE 2 bco270014-tbl-0002:** Details of measures and outcomes collected within patient questionnaires.

		Baseline	Immediate after consultation	3 months after consultation
**Sociodemographic**				
Age	10‐year age groups	•		
Sex	Female/Male/Prefer not to specify	•		
Gender	One question on whether the participant identifies with the same gender as sex registered at birth	•		
Ethnicity	Four categories plus Other/Prefer not to specify	•		
Postcode		•		
**Understanding of risk of recurrence**				
Subjective risk comprehension	Two questions on 7‐point scales		•	
Objective risk comprehension	Risk category and numeric 1–100 range		•	•
Risk conviction for numeric risk of recurrence	Two questions on 7‐point confidence scales^25^		•	•
Relative risk of recurrence and death from other causes	5‐point relative scale		•	•
Risk conviction for relative risk of recurrence and death from other causes	Two questions on 7‐point confidence scales^25^		•	•
**Understanding of follow‐up**				
Subjective Follow up Comprehension	Two questions on 7‐point scales		•	
**Fear of recurrence**				
Fear of recurrence	Fear of Cancer Recurrence Inventory short form (FCRI‐SF).^24^		•	•
**Satisfaction**				
Satisfaction with risk information	Two questions on 7‐point agreement scales		•	
Satisfaction with Follow up Information	Three questions on 7‐point agreement scales		•	
Overall Satisfaction with consultation	7‐point agreement scale		•	
**Views of the report** *****				
Feeling	7‐point satisfaction scale		•	
Layout	7‐point satisfaction scale		•	
Information	7‐point satisfaction scale		•	
**Moderators**				
Subjective numeracy	Eight questions on 6‐point scale, taken from the cognitive ability domain of the Subjective Numeracy Scale^22^	•		
Objective numeracy	Three questions with numeric answers^23^	•		
Health Literacy	Single Item Literacy Screener (SILS)^21^	•		
General Health	EQ‐5D‐5L^24^	•		

*
Intervention group only.

Three months after their consultation, study participants in both arms will be sent a final short questionnaire including measures of perceived risk of cancer recurrence and the complete Fear of Cancer Recurrence Inventory short form (FCRI‐SF) (Table 2, File S3).

To assess the fidelity of the use of the tool by clinicians and to monitor the additional time taken to deliver the intervention, a subset of both control and intervention consultations will be video recorded. A subset of study participants from the intervention arm will additionally be purposively sampled based on risk profile to take part in a telephone or online interview with a member of the research team within 2–6 weeks of their consultation. The interviews will be semi‐structured based on an interview schedule informed by the Theoretical Framework of Acceptability (TFA)^27^ and will include a discussion of the participants' experience of being told their risk of recurrence and competing risk of death from other causes using the PREDICT Kidney tool and how this has affected their understanding of their risk of recurrent disease.

All healthcare professionals participating in this study will also be invited to participate in an interview with a member of the research team. The interviews will be based on a schedule informed by the TFA,^27^ normalisation process theory^28^ and the system usability scale.^29^ They will focus on tool acceptability, perceived usability and perceived limitations and barriers to uptake.

### Analysis

5.5

Descriptive statistics will be used to summarise recruitment into the study, characteristics of the study population at baseline, completeness of the questionnaires and quantitative measures within the questionnaires. Means and standard deviations will be used for normally distributed continuous variables, medians and interquartile range for non‐normally distributed continuous variables and numbers and percentages for categorical variables. Where reported, all proportions will be presented with 95% confidence intervals.

The impact of the PREDICT Kidney tool on patient‐level clinical outcomes will be tested first in an intention‐to‐treat analysis comparing the intervention group to the control group. A secondary *per protocol* analysis will then be performed. In both cases, for continuous outcome measures (satisfaction, fear of cancer recurrence and risk conviction), mean scores between groups at both time points will be compared using mixed linear regression models, adjusting for risk category and accounting for clustering within each site. All models will be adjusted for age, ethnicity, deprivation and EQ‐5D‐5L. The size of the difference between groups will be interpreted by comparison with the standard deviation (SD), with the criteria for clinically relevant change being a change of 0.5 SD. Exploratory subgroup analyses will be performed by the site to assess whether the location of the study had any impact on outcomes and to assess the variance of the outcomes, by the patient's risk category of recurrence and by age. Accuracy of perceived risk will be analysed as a binary outcome using logistic regression, again adjusted for risk category, clustering within each site and age, ethnicity, deprivation and EQ‐5D‐5L. Statistical significance will be p < 0.05. All analyses will be conducted in STATA 14 or R.

Audio from the video‐recorded consultations and interviews will be transcribed verbatim before analysis. Qualitative data from the semi‐structured interviews will be analysed using a mix of inductive and deductive Thematic Analysis. The inductive analysis will look for emergent themes relevant to the study aims and the deductive thematic analysis will be organised around the seven dimensions of the Theoretical Framework of Acceptability.^27^ Qualitative data from recorded consultations in the intervention arm will be used to assess clinician adherence to a fidelity checklist based on the ‘best practice’ guidance document provided to clinicians and the length of consultations.

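### Numeracy and health literacy are collected at baseline as moderators but appear in no stated covariate or subgroup list, leaving a non-randomised comparison of risk understanding partly open to confounding by them

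*Protocol article*

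**What the plan says.** Table 2 groups four baseline measures under the heading Moderators: subjective numeracy (eight questions), objective numeracy ("Three questions with numeric answers"), health literacy (the one-item SILS) and general health (EQ-5D-5L).

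Section 5.5 (Analysis) then fixes the models. The continuous outcomes it names are "satisfaction, fear of cancer recurrence and risk conviction". They are compared by mixed linear regression, "adjusting for risk category and accounting for clustering within each site". It continues: "All models will be adjusted for age, ethnicity, deprivation and" EQ-5D-5L. For understanding, "Accuracy of perceived risk will be analysed as a binary outcome using logistic regression", and the same covariates are listed again. On subgroups: "Exploratory subgroup analyses will be performed by the site", and further "by the patient's risk category of recurrence and by age".

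Section 5.1 fills the standard-care arm first at each site, to a minimum of eight patients, and then sends all later patients to the intervention arm. Table 2 marks the understanding and conviction measures only after the consultation. Section 5.5 tests the effect of the tool at p < 0.05 and reads differences between groups against 0.5 SD.

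**The concern.** The tool conveys absolute risks as numbers and graphics, and objective comprehension asks the patient for a risk category and a number. Of the baseline measures collected, numeracy is the one most directly tied to that task. It is measured and labelled a moderator, yet the stated analysis gives it no role as covariate, subgroup or interaction. Of the four measures under that heading only EQ-5D-5L is used.

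In a randomised trial this would cost mainly some precision. Here the arms are consecutive cohorts, so nothing in the design balances numeracy between them, and no baseline value of the outcome can stand in for it. If the later cohort happened to be more numerate, part of the difference in understanding could be credited to the tool and carried into the design estimates for the future trial. The study would also say nothing about whether less numerate patients fare differently with the tool, which is what the Moderators label suggests it was meant to explore.

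**Working it through.** **The lists side by side**

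- Moderators (Table 2): subjective numeracy, objective numeracy, health literacy, EQ-5D-5L.
- Covariates (section 5.5): age, ethnicity, deprivation, EQ-5D-5L, risk category, with site clustering.
- Subgroups (section 5.5): site, risk category, age.
- Overlap of the moderators with the other two lists: EQ-5D-5L only, as a covariate.

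The plan gives no figure on numeracy that could be reproduced. Its one precision statement concerns the recruitment rate and does not bear on this point. What follows is an illustration of size.

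**Inputs**

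- 30 patients per arm (section 5.3); 0.5 SD as the relevant difference (section 5.5).
- Correlation r between numeracy and a continuous outcome score: not in the documents; assumed 0.2 to 0.5.

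**Chance imbalance**

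- SE of a standardised baseline difference = sqrt(1/30 + 1/30) = 0.258 SD.
- If standard care stops at its minimum of 3 × 8 = 24 and 60 are recruited in all: sqrt(1/24 + 1/36) = 0.264 SD, almost the same.
- At 30 v 30, chance alone gives an imbalance above 0.25 SD in about 33% of such studies and above 0.5 SD in about 5%.

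**Shift in a continuous outcome** = r × imbalance, before any absorption by other covariates

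- 1 SE: 0.2 × 0.258 = 0.05 SD to 0.5 × 0.258 = 0.13 SD, which is 10% to 26% of 0.5 SD.
- 2 SE (0.516 SD): 0.2 × 0.516 = 0.10 SD to 0.5 × 0.516 = 0.26 SD, which is 21% to 52% of 0.5 SD.
- If the existing covariates absorbed, say, 15% (an assumption), the 2-SE shift would be 0.85 × 0.103 = 0.09 SD to 0.85 × 0.258 = 0.22 SD.

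**Precision**

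- Adjustment removes r² of the residual variance: 0.2² = 4% to 0.5² = 25%.
- Approximate power for 0.5 SD at 30 per arm rises from 49% to between 51% and 61%, ignoring clustering and lost degrees of freedom.

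**Why a formal moderator test is not the remedy**

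- With an even split into lower and higher numeracy there are four cells of 15. The SE of the difference between the two tool effects is sqrt(4/15) = 0.516 SD, about the whole of the 0.5 SD criterion. Description is what the data can support.

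**The case against.** Several points against the concern are sound, and they limit it.

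- A reader might infer that a numeracy imbalance passes unchanged into the results. The documents do not support that. The models already adjust for age, ethnicity, deprivation, EQ-5D-5L and risk category, and some of these may absorb part of it. How much cannot be told from the documents.
- A reader might apply the 0.5 SD comparison to all comprehension outcomes. The only understanding outcome with a named model is accuracy of perceived risk. It is binary, so neither the SD shifts nor the variance reduction applies to it. Subjective comprehension has no named model in section 5.5.
- A reader might take the 2-SE case as typical, or as bias. It is roughly a 5% tail event, and chance imbalance is ordinary sampling error already reflected in the confidence interval. What is particular to this design is drift between periods, which the interval does not cover. The documents give no figure for drift and no evidence that numeracy drifts over the planned September 2024 to July 2025 period.
- The items are not simply thrown away. Section 5.5 summarises baseline characteristics and questionnaire measures descriptively, which can include numeracy and SILS, although it does not say by arm.
- With 60 patients a short covariate list is defensible, and the Discussion concedes that the study is too small to show improved understanding of follow-up or reduced fear of recurrence.

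What stands is narrower. The covariate list is stated for all models and repeated for the logistic model, so this is a choice the article makes and not a detail left to an analysis plan. It sits badly with the Moderators heading, with sequential allocation and with a planned significance test.

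**Conclusion.** The point holds in moderate form. Three measures labelled as moderators have no place in the stated covariate or subgroup lists, in a comparison where neither randomisation nor a baseline outcome value guards against a numeracy difference between cohorts. Some confounding of the understanding outcomes is possible, limited by whatever the existing covariates absorb.

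On a continuous score such as risk conviction, the plausible shift is about 0.05 to 0.13 SD for a 1-SE imbalance and 0.10 to 0.26 SD for a 2-SE imbalance. This rests on the assumed correlation of 0.2 to 0.5, on 30 per arm and on no absorption by other covariates. No figure is offered for the binary accuracy outcome or for period drift. The feasibility aims do not depend on this point; the between-arm estimates of understanding do. It should be corrected, but it is not fatal.

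**What to change.** In section 5.5:

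1. Add the objective numeracy score, with its scoring stated, as one linear term in the models for accuracy of perceived risk and risk conviction, and in whatever model is used for subjective comprehension once one is named. Keep the existing covariates. Dropping ethnicity to make room would remove a planned confounder from a non-randomised comparison, and the documents give no ground for that.
2. If the logistic model becomes too sparse, keep it as planned and report the numeracy-adjusted version as a prespecified sensitivity analysis.
3. Tabulate numeracy and SILS by arm.
4. Report the understanding outcomes descriptively for lower and higher numeracy, without a test of interaction.

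The cost is a change of wording, since the data are already being collected, plus one degree of freedom per model and the loss of a few patients who leave the numeracy questions unanswered.

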Participants will be then allocated to the ‘standard of care’ (SOC) arm or the ‘SOC and PREDICT Kidney’ (intervention) arm of the study (Figure 1). Allocation will be done such that patients at each site will be allocated to the SOC arm until a minimum of eight patients have been recruited. Subsequently, patients at each site will be allocated to the intervention arm. This approach has been chosen to reduce contamination between the arms by clinicians changing their SOC following participation in the intervention arm of the study.

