## DISCUSSION

6

Variations in current practice and the need for improved, consistent communication about the risk of recurrence of localised RCC following surgery have been identified by patients.^15^ The value of basing follow‐up care on individual‐level estimated risk of recurrence and considering competing risks has also been identified by researchers and clinicians.^11^ PREDICT Kidney is a new online tool developed to enable the estimation of these risks and to support clinicians to communicate the risk of recurrence so that patients feel more informed and have a better understanding of the rationale behind the planned follow‐up. While the use of risk prediction models to inform kidney cancer follow‐up regimes is recommended in current clinical guidance, to our knowledge, this is the first study to assess the use of a risk communication tool within routine care with this patient population.

A key strength of this study is the use of a tool that employs a well‐established risk model, the Leibovich model,^12^, ^30^, ^31^ employs visual aids to simplify communication of complex information in line with best practice,^32^ and has been developed with extensive input from those with experience of kidney cancer, members of the public and clinicians. By presenting an individual patient's estimated risk of death from other causes alongside their estimated risk of recurrence, our hypothesis is that the tool will facilitate more informed discussions around follow‐up care and encourage consideration of the whole person by the clinical team rather than the current RCC‐centric approach. While this study, given its size, will not enable us to demonstrate whether the use of the tool improves patient understanding of follow‐up or reduces fear of recurrence, the data collected will enable us to assess the feasibility and acceptability of incorporating the PREDICT Kidney online tool into the first post‐surgery follow‐up appointment for patients with localised RCC. In preparation for designing a future trial using this tool, we will evaluate participant recruitment, completeness of data collection and estimates of patient‐level outcomes.

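### Section 5.5 tests the tool's impact at p < 0.05, but arm is confounded with calendar period at every site and the discussion concedes that an effect on a tested outcome cannot be shown

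*Protocol article*

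**What the plan says.** Section 5.5 states that the tool's effect on patient-level outcomes "will be tested first in an intention‐to‐treat analysis comparing the intervention group to the control group", followed by a per-protocol analysis. It specifies that "for continuous outcome measures (satisfaction, fear of cancer recurrence and risk conviction), mean scores between groups at both time points will be compared" with mixed linear models, and that accuracy of perceived risk is analysed by logistic regression. All models adjust for risk category, age, ethnicity, deprivation and EQ-5D-5L and account for site. Differences are interpreted against the standard deviation, "with the criteria for clinically relevant change being a change of 0.5 SD". The section then sets the rule "Statistical significance will be p < 0.05". Only the subgroup analyses (site, risk category, age) are labelled exploratory.

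Section 5.1 allocates patients at each site to standard care until at least eight have been recruited. "Subsequently, patients at each site will be allocated to the intervention arm". The stated reason is to limit contamination. Section 5.3 aims for 30 per arm and justifies this by the precision of the recruitment rate and the needs of the qualitative work. Section 3 gives the patient-level aim as estimates to inform a future trial. The Discussion states a limit: "While this study, given its size, will not enable us to demonstrate whether the use of the tool improves patient understanding of". That sentence then names two constructs: how well patients understand their follow-up, and their fear of recurrence.

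**The concern.** The analysis section sets a confirmatory rule for a comparison that the rest of the article treats as estimation. For fear of recurrence the conflict is direct: the outcome is tested in section 5.5 and conceded in the Discussion. Satisfaction, risk conviction and accuracy of perceived risk are not named in that concession, but they come from the same patients and the same allocation, so the same limits apply.

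The Discussion gives only size as the limit. The sequential allocation is a separate limit of a different kind. Any change between the two periods at a site (staff, clinic practice, case mix, who agrees to take part) falls entirely on the arm contrast. A larger sample would estimate that mixture more precisely without separating its parts. The planned covariates describe patients, not periods, so adjusting for them does not remove the confounding.

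The risk is that a chance result or a period difference is reported as a significant effect of the tool.

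**Working it through.** **Inputs.** From the article: 30 per arm (5.3), significance at 0.05 and relevance at 0.5 SD (5.5), outcomes and time points (5.5, Tables 1 and 2), sequential allocation (5.1). Assumed: two-sided tests, no loss to follow-up, no gain or loss from covariates or site clustering, and the period shifts in step 5.

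**1. The plan's own figure.** With 60 consenting at 50% uptake, 60/0.5 = 120 are invited. The half-width is 1.96 × √(0.25/120) = 0.089, or 8.9 points. This is within the stated ±10%, so the sample-size statement is reproduced. It concerns recruitment only.

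**2. Precision of a mean difference, in SD units.** SE = √(2/30) = 0.258. With t(0.975, 58 df) = 2.002, the half-width is 2.002 × 0.258 = 0.517 SD. An observed difference of exactly 0.5 SD gives t = 0.5/0.258 = 1.94 and p = 0.058. The relevance criterion and the significance rule can therefore disagree at the threshold itself.

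**3. Power for a true 0.5 SD difference.** Noncentral t with 58 df and noncentrality 1.94 gives 47.8%. By the normal approximation it is 49% with no loss, and 45%, 41% and 37% with assumed losses of 10%, 20% and 30%. By the same approximation, 80% power would need 63 per arm, and 30 per arm has 80% power only for 0.72 SD.

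**4. Chance of at least one p < 0.05 with no true effect and no period difference.** Intention-to-treat set only. Independent tests: 1 − 0.95^k. Correlated tests: simulation with pairwise correlation 0.5.

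| Reading | Count | Independent | Correlation 0.5 |
|---|---|---|---|
| Fewest tests from 5.5: satisfaction 1, fear 2, conviction 2, accuracy 1 | 6 | 26% | 21% |
| Table 2 scales counted separately: satisfaction 3, fear 2, conviction 4, accuracy 2 | 11 | 43% | 30% |

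The per-protocol and subgroup repeats would add to these.

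**5. Period shift with no tool effect.** A shift of b SD between periods enters the test as noncentrality b/0.258. The article gives no figure for b, so these values are assumptions.

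| Assumed shift | Noncentrality | Chance of p < 0.05, one outcome |
|---|---|---|
| 0.2 SD | 0.77 | 12% |
| 0.3 SD | 1.16 | 21% |
| 0.5 SD | 1.94 | 48% |

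Unlike the figures in step 4, these rise as the sample grows.

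**The case against.** The strongest reply is that the article is open about what it is. It calls itself a feasibility study, lists the feasibility objectives first, states the sequential allocation and its reason, delays clinician training until control recruitment is complete, and leaves efficacy to a later randomised trial. The 0.5 SD criterion also directs attention to effect size and not to p alone. All of that is true. It does not answer the point, because section 5.5 still tests impact with a significance rule and labels only the subgroups exploratory.

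The numbers have limits too. Eleven tests is a high reading, which is why six is shown beside it. The half-width of 0.517 SD is unadjusted. If the covariates explained about 7% of the variance it would be 0.517 × √0.93 = 0.50 SD, ignoring site effects and lost degrees of freedom. That leaves it about as wide as the criterion.

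A reader might infer several stronger charges that the article does not support:

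- *That no SDs will be available for planning.* Section 5.5 compares means, interprets differences against the SD and looks at outcome variance by site. The median and interquartile range rule concerns descriptive summaries.
- *That feasibility outputs are secondary.* Section 5.5 opens with recruitment and completeness, and promises 95% intervals for proportions.
- *That the intention-to-treat label hides the design.* Section 5.1 states the allocation plainly, and the term can simply mean analysed as allocated.
- *That missing multiplicity control is a fault in itself.* An article may leave that to an analysis plan that is not shown here. The counts above only indicate how the single rule would behave.

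**Conclusion.** The point holds. A p < 0.05 rule for the tool's impact does not fit a non-randomised sequential comparison sized for recruitment and intended for estimation. The contradiction with the Discussion is direct for fear of recurrence. For the other tested outcomes it follows from the same size and allocation, and the article should not be read as conceding that nothing about the tool can be shown.

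At 30 per arm, power for 0.5 SD is about 48% and the interval is about ±0.52 SD before adjustment, clustering and loss. The chance of a spurious significant result somewhere is 21–26% on the narrowest count and 30–43% on the widest, with no period effect at all. How large a period effect might be is unknown; the 12%, 21% and 48% figures only show its consequence if it were 0.2, 0.3 or 0.5 SD. The absence of period confounding from the stated limitations is the more important omission, since more patients would not cure it. The recruitment-precision statement is not in error.

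**What to change.** In section 5.5, delete the significance criterion and the wording that impact is tested. Report adjusted between-group differences with 95% confidence intervals, described as exploratory estimates from a non-randomised comparison of different patients in successive periods at each site. Read the interval, and not only the point estimate, against ±0.5 SD. Tabulate the SD of each continuous outcome beside its difference, whatever summary is used for skewed scales. In the Discussion, add period confounding to size as a reason why no effect can be claimed, and extend the statement to all patient-level outcomes.

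The cost is wording. No patients, data or visits change. The downside is that no significant finding can be claimed, which the Discussion already gives up for two of the constructs.
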